### 2.5. Voice recording protocol

Voice recordings will be obtained using a Jabra Speak 510 USB omnidirectional microphone, positioned frontally at a distance of no more than 20 cm from the participant’s mouth. Recordings will be conducted in a quiet hospital room, with minimized background noise, closed doors and windows whenever feasible, silenced electronic devices, and no overlapping speech or external interruptions whenever possible.

The Jabra Speak 510 microphone was selected for pragmatic and translational reasons: it is affordable, widely available, easy to deploy and compatible with routine hospital use. This choice prioritizes ecological validity over laboratory-grade audio fidelity, which may reduce the precision of signal-sensitive measures such as jitter, shimmer, HNR, and intensity. This potential variability will be reduced by maintaining the same microphone, configuration, placement, and recording conditions throughout the study. This approach is consistent with previous studies that have used non-specialized recording devices, including tablet microphones, smartphone microphones and mobile phones, to extract clinically relevant speech and voice features [19,24,25,30].

Repeated assessments will be scheduled within a similar time-of-day window for each participant whenever feasible. Because recordings are integrated into routine clinical visits, exact consistency cannot be guaranteed; recording time will therefore be documented and considered in sensitivity analyses. Audio recordings will be stored in uncompressed WAV format to preserve signal integrity during feature extraction. All files will be labeled using pseudonymized alphanumeric identifiers. Speaker diarization will identify participant and interviewer segments, followed by manual review. Overlapping or uncertain segments will be excluded, and the original recording will be preserved unchanged. For acoustic and paralinguistic analyses, only participant speech will be retained. The complete interaction will be automatically transcribed and manually reviewed to correct transcription and speaker-attribution errors. Linguistic variables and contextual text embeddings will be extracted from the reviewed participant transcripts, while interviewer turns will be retained as conversational context.

For each recording, total recording duration, cumulative valid participant-speech duration, silence-to-speech proportion, number of intelligibly transcribed words, and relevant recording incidents will be documented. A minimum of two minutes of cumulative valid participant speech will be required for the primary multimodal analysis. consistent with previous studies using short samples [11,19]. Recordings below this threshold will be considered non-evaluable for that analysis, but the participant will not be excluded from the study.

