### 2.3. Study procedures and visit schedule

Participants will be recruited consecutively according to eligibility criteria. Patients will be invited by physicians from the research team during routine clinical practice. Healthy controls will be invited by members of the research team and, if they agree to participate, will be referred to a physician from the research team for baseline assessment. As this is an observational study, no randomization or blinding procedures will be applied.

At the baseline visit (V0), all participants will receive verbal and written information about the study objectives, methodology, non-invasive nature of the procedures, confidentiality safeguards, and exclusive research use of the collected data. Written informed consent will be obtained before any study-related procedure. A clinical interview will then be conducted to collect baseline sociodemographic and clinical information, followed by psychometric assessment using the clinical instruments specified in the protocol. During the same session, voice recordings will be obtained under standardized conditions.

Only patients with depressive disorder will undergo longitudinal follow-up. Patients will attend four additional visits coinciding, whenever possible, with routine psychiatric follow-up visits: V1 at 30 days, V2 at 60 days, V3 at 90 days and V4 at 120 days, each with an allowed window of ±7 days. At each follow-up visit, the same recording and clinical assessment procedures applied at baseline will be repeated. Clinician-rated and self-reported measures of depressive severity will be updated, and relevant clinical changes, including treatment adjustments or adverse events, will be documented. Healthy controls will complete only the baseline visit under the same recording conditions.

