### 2.4. Sample size and sampling strategy

The planned study sample comprises 75 participants: 25 patients with a clinical diagnosis of moderate or severe unipolar depression and 50 healthy controls. Patients will be assessed at five time points: baseline (V0) and four monthly follow-up visits at 30, 60, 90 and 120 days, each with an allowed window of ±7 days. Assuming complete follow-up, this will generate 125 longitudinal voice recordings in the clinical group. Healthy controls will undergo a single baseline assessment, generating 50 voice recordings. The planned dataset therefore comprises 175 voice recordings.

The sample size was defined pragmatically as a feasible recruitment target for a hospital-based feasibility and methodological pilot study conducted in a real-world clinical setting. The study is not intended as a definitive diagnostic accuracy trial powered to estimate the performance of a final clinical classifier. Rather, it is designed to evaluate the feasibility, standardization, reproducibility and analytical validity of a multimodal voice- and speech-based methodology for depression assessment and longitudinal monitoring.

As a quantitative sensitivity analysis, a baseline comparison of 25 patients and 50 healthy controls, with a two-sided significance level of 0.05 and 80% power, would detect a standardized mean difference of approximately Cohen’s d = 0.70. The study is therefore primarily sensitive to moderate-to-large effects. This is presented as a sensitivity analysis because reliable prospective effect-size estimates are not available for the multiple exploratory speech-derived variables included.

The sampling strategy will be consecutive and non-probabilistic. Eligible patients will be recruited during routine clinical care in the Department of Psychiatry, including both outpatient consultations and inpatient care. Healthy controls will be invited by members of the research team and assessed after confirmation of eligibility.

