Although a balanced baseline comparison between patients and healthy controls would be methodologically desirable, the final allocation was defined according to feasibility considerations. Healthy controls will be individually matched to patients by age and sex whenever feasible. If individual matching cannot be achieved, control recruitment will be guided by the age and sex distribution of the patient group to obtain group-level frequency matching as closely as possible. Recruitment of clinically characterized patients with moderate or severe depressive disorder is expected to be more demanding because it requires repeated clinical assessments and longitudinal follow-up. In contrast, healthy controls require only a single baseline visit, allowing the inclusion of a larger control group without substantially increasing study burden. Therefore, the study will include 25 patients and 50 healthy controls. This design is expected to strengthen the baseline characterization of non-depressed speech patterns while preserving the longitudinal focus of the clinical cohort.

At participant level, baseline analyses will compare patients and healthy controls, whereas longitudinal analyses will focus on within-patient changes across repeated assessments. For predictive modeling, the imbalance between groups will be explicitly considered through appropriate analytical strategies, such as participant-level data splitting, balanced resampling, class weighting or sensitivity analyses when applicable.

Given the pilot nature of the study and the moderate sample size, classifier performance estimates will be interpreted as exploratory and hypothesis-generating. The study will prioritize transparent feature extraction, reproducible preprocessing, clinically interpretable modeling and longitudinal within-subject analysis over the development of a definitive deployable diagnostic model. Model complexity will be limited in relation to the available sample size, and classifier performance estimates will be accompanied by confidence intervals whenever feasible.

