### 2.6. Variables

All study variables will be recorded in a pseudonymized case report form developed specifically for the VOICE-DEP study. Variables will be classified into: (i) baseline variables collected only at V0, and (ii) longitudinal visit variables collected at V0, V1, V2, V3 and V4 in patients with depressive disorder.

Exposure variable: The main exposure variable is the medical diagnosis of moderate or severe unipolar depressive disorder, with or without psychotic symptoms, according to the predefined ICD-10 categories included in the protocol.

Primary outcome variables: The primary outcome variables are the standardized voice recording and the multimodal speech- and speech-derived variables extracted from the recorded clinical interview. These variables will be grouped into acoustic, paralinguistic and linguistic domains.

Clinician-rated and self-reported symptom variables: At each study visit, depressive symptom severity and global clinical status will be assessed concurrently with the voice recording using the MADRS, the Clinical Global Impression scale (CGI), and the Patient Health Questionnaire-9 (PHQ-9). These variables will provide the clinical reference outcomes for cross-sectional and longitudinal analyses. Psychotic depression, operationally defined by an ICD-10 diagnosis of F32.3 or F33.3, will be recorded as a binary clinical variable. The same clinician-rated and self-reported assessments will also be conducted in healthy controls at baseline (V0) to identify possible subthreshold symptoms.

Baseline and longitudinal variables: Baseline variables collected at V0 will include demographic, anthropometric, clinical and contextual information, including psychiatric and medical history, substance use, stressful life events, and previous depressive episodes. Longitudinal variables collected across visits will include recording traceability variables, symptom scales, pharmacological treatment variables, psychotherapy variables and neurostimulation-related variables.

Metadata related to the recording process, including pseudonymized audio identifiers and recording incidents, will also be documented for traceability and quality control purposes.

The complete list of study variables operationalized in the VOICE-DEP case report form is summarized in Table 2. The list of multimodal voice- and speech-derived variables is summarized in Table 3.

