**Table 2 pone.0353827.t002:** Study variables recorded in the VOICE-DEP case report form and assessment schedule.

Domain	Description	Assessment visits
Participant identification	Participant category (patient or control), study code, and visit date	V0–V4 in patients; V0 in controls
Sociodemographic and anthropometric baseline variables	Sex, age, marital status, place of residence, birth order in the sibship, height, weight, body mass index, body surface area, educational level, childcare responsibilities, caregiving responsibilities for dependent relatives, religious belief, community religious practice, and social relationships	V0 only
Lifestyle, family history and contextual baseline variables	First-degree family psychiatric history, toxic habits, tobacco, alcohol, cannabis, cocaine, amphetamine and other substance use, physical activity, diet pattern, complementary or alternative treatments and specific prescribed diets, pharmacogenetic or pharmacodynamic isoform information when available, employment status, night work, acute and chronic stressful life events, and current and lifetime traumatic events	V0 only
Clinical baseline variables	Principal diagnosis according to ICD-10 depressive categories, psychiatric comorbidities, medical comorbidities, previous suicidal ideation, previous suicidal behavior, previous self-harm, duration of the current episode, time since initial diagnosis, and number of previous depressive episodes	V0 only
Recording and audio traceability variables	Whether the voice recording was obtained, pseudonymized audio file identifier, presence of recording incidents, and type of incident (patient need, clinical need, technical problem, others)	V0–V4 in patients; V0 in controls
Clinician-rated and self-reported symptom variables	Depressive symptom severity assessed with MADRS, global clinical impression assessed with CGI, and self-reported depressive symptom burden assessed with PHQ-9	V0–V4 in patients; V0 in controls
Pharmacological treatment variables	Pharmacological treatment received, including total daily dose in mg/24h, dosing interval, administration time, and duration of treatment at the recorded dose	V0–V4 in patients
Non-pharmacological treatment and psy-chotherapy variables	Sleep hygiene measures, diet pattern, regular physical activity, discontinuation of toxic habits, psychotherapy attendance, psychotherapy type, and psychotherapy frequency	V0–V4 in patients

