### 2.7. Statistical and analytical plan

The analytical strategy of the VOICE-DEP study is designed to support the primary and secondary objectives of the protocol while ensuring methodological transparency, reproducibility, and robustness. In accordance with the study design, the analysis will address three complementary dimensions: (i) descriptive characterization of the study sample and extracted variables, (ii) exploratory cross-sectional association and discrimination analyses between patients with depressive disorder and healthy controls, and (iii) longitudinal intra-individual modeling of changes in voice- and speech-derived variables in relation to clinical evolution.

First, a descriptive analysis will be performed for all study variables recorded in the case report form. Quantitative variables, including acoustic, paralinguistic, and linguistic features, will be summarized using means and standard deviations or medians and interquartile ranges, as appropriate according to their distribution. Qualitative variables will be described using absolute frequencies and percentages. This descriptive phase will include both baseline variables collected at V0 and longitudinal variables collected across repeated visits in patients. Age, sex, educational level and available socioeconomic-related variables will be compared between groups and considered as covariates in adjusted or sensitivity analyses when relevant imbalance is observed and the sample size permits stable estimation.

Second, the association between continuous voice- and speech-derived digital biomarkers and clinical severity measures will be explored using Pearson or Spearman correlation coefficients, depending on distributional assumptions. These analyses will focus on the relationship between multimodal voice-derived variables and clinician-rated depressive symptom severity measured with the MADRS, global clinical status measured with the CGI, and self-reported depressive symptom burden measured with the Patient Health Questionnaire-9 (PHQ-9).

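### Recording hour is aligned across a patient's own visits but not between patients and controls, so the V0 group contrast could carry a time-of-day difference

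*Protocol article*

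**What the plan says.** The scheduling rule is in section 2.5: "Repeated assessments will be scheduled within a similar time-of-day window for each participant whenever feasible". The same paragraph concedes that routine visits prevent exact consistency and adds that "recording time will therefore be documented and considered in sensitivity analyses". Section 3.1 names residual variability by time of day as a limitation.

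For controls, section 2.3 states: "Healthy controls will complete only the baseline visit under the same recording conditions". Section 2.4 gives the matching factors: "Healthy controls will be individually matched to patients by age and sex whenever feasible", with frequency matching on the same two factors as the fallback. For the group comparison, section 2.7 says: "Age, sex, educational level and available socioeconomic-related variables will be compared between groups and considered as covariates in adjusted or sensitivity analyses", subject to relevant imbalance and stable estimation. Recording hour is not in that list.

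On data capture, section 2.6 says: "The complete list of study variables operationalized in the VOICE-DEP case report form is summarized in Table 2". The traceability row of that table reads: "Whether the voice recording was obtained, pseudonymized audio file identifier, presence of recording incidents, and type of incident". The table also has the visit date, but no clock time for the recording. The per-recording items at the end of section 2.5 (durations, silence proportion, word count, incidents) do not include it either.

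**The concern.** The plan accepts that the hour of recording can move voice measurements, and it controls the hour in one direction only. The rule keeps a patient's V0 to V4 recordings comparable with each other. It cannot make a control's one recording comparable with a patient's V0 recording.

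The two groups also reach the recording room by different routes. Patients are recorded during routine outpatient or inpatient care; controls are invited by the research team and referred to a physician for one visit. Two separate scheduling processes, with no rule linking them, leave room for different hours.

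At stake is the V0 patient-control comparison. Discrimination between the groups is part of the primary objective in section 2.1, and section 2.4 names standardization and analytical validity among the things the pilot is meant to evaluate. A difference in recording hour would enter the feature differences and the AUC looking like an effect of depression. Recruitment opened on 2026/05/21 according to section 2.10, and a control's only session cannot be moved to another hour afterwards.

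**Working it through.** **1. The plan's own figure.** Section 2.4 considers "a baseline comparison of 25 patients and 50 healthy controls, with a two-sided significance level of 0.05 and 80% power" and states a detectable d of about 0.70.

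- Standard error in SD units: √(1/25 + 1/50) = √0.06 = 0.245.
- Normal approximation: (1.960 + 0.842) × 0.245 = 0.686. With the t distribution the detectable d is 0.695.
- Power at d = 0.70 is 0.815 (normal) or 0.805 (t).

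The stated figure reproduces and is not in dispute. It serves below as a yardstick.

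**2. What could align recording hour between groups at V0.**

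| Possible safeguard | Where | Covers the V0 group contrast? |
|---|---|---|
| Similar time-of-day window | 2.5 | No: repeated assessments only |
| Matching | 2.4 | No: age and sex |
| Named covariates | 2.7 | No: recording hour not named |
| Sensitivity analyses on recording time | 2.5 | Not stated either way |
| Stated limitation | 3.1 | Acknowledges; does not align or adjust |

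**3. Possible size.** The documents give neither the effect of time of day on any feature nor the recording hours of either group. Both inputs below are assumptions.

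- g = shift in a feature between morning and afternoon, 0.2 to 0.5 SD.
- Δ = difference between groups in the share of morning recordings, 0.20 to 0.60.

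With no true group difference, the expected unadjusted difference is bias = g × Δ. For one feature, the two-sided false-positive rate at 0.05 follows from a noncentral t with 73 degrees of freedom and noncentrality bias/0.245. The single-feature AUC is Φ(bias/√2). Both take the feature's SD as 1.

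| g | Δ | Bias (SD) | Share of 0.70 | False-positive rate | AUC with no true difference |
|---|---|---|---|---|---|
| 0.2 | 0.20 | 0.04 | 6% | 5.3% | 0.51 |
| 0.3 | 0.40 | 0.12 | 17% | 7.7% | 0.53 |
| 0.5 | 0.40 | 0.20 | 29% | 12.7% | 0.56 |
| 0.5 | 0.60 | 0.30 | 43% | 22.7% | 0.58 |

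The first row is negligible, the second modest, and the last is the extreme corner where both assumptions are at their maximum. If Δ = 0, the bias is zero whatever g is.

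**The case against.** The best defence is that the plan already deals with recording time. Section 2.5 promises to document it and consider it in sensitivity analyses, without restricting these to longitudinal data, and section 3.1 lists it as a limitation. Controls are recorded under the same conditions as patients, in the same hospital setting. Classifier results are declared exploratory, and the study is a pilot. With 25 patients, handling recording hour by sensitivity analysis is a defensible choice.

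Most of this stands, and it rules out several stronger readings that a reader might infer.

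- *That the groups will be recorded at different hours.* No passage gives hours for either group. Separate scheduling routes make a difference possible and no more.
- *That recording times are going uncollected, because Table 2 has no field for them.* Section 2.5 says they are documented. Table 2 is a summary, and it also omits other items that are to be documented, such as valid-speech duration and word count. The metadata sentence in section 2.6 is open-ended. This is a mismatch of wording between sections 2.5 and 2.6. For the same reason the text does not support saying that time since a drug dose could not be derived, and no analysis of it is planned.
- *That the sensitivity analyses are longitudinal only.* The preceding sentence is about repeated assessments, which makes the scope unclear, but the text sets no such limit.
- *That time band must enter the main patient-control model.* That would be a trade-off against the limit on model complexity in section 2.4 and the covariate conditions in section 2.7.

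What the defence does not answer is design. The same-conditions phrase does not mention the hour, and section 2.5 handles time of day by its own rule, which leaves controls out. A sensitivity analysis works only as far as the two groups' hours overlap, and overlap is settled when sessions are booked.

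**Conclusion.** The point holds as a gap in standardization that is inexpensive to close. Nothing in the plan aligns recording hour between patients and controls at V0, so that contrast could carry a time-of-day difference if the hours differ. The mid-range figure of 0.12 SD, about a sixth of the detectable 0.70, is a fair illustration; the 0.30 SD corner should not be read as an expectation. All sizes rest on assumed values of g and Δ and describe an unadjusted comparison of one feature. The missing Table 2 field and the unstated scope of the sensitivity analysis are clarifications. The scheduling of controls is the substantive part, because it cannot be repaired after a control's single session.

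**What to change.** 1. In section 2.5, add that control sessions will, whenever feasible, be scheduled in a time-of-day band similar to that of the matched patient's V0 recording or, under frequency matching, to the overall distribution of patients' V0 recording times.
2. In the same section, state that the sensitivity analysis on recording time includes the V0 patient-control contrast.
3. In the traceability row of Table 2, list recording start time for both groups.

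The cost is slightly less flexible scheduling of controls, one listed field and one sentence of analysis text. Sample size and power are unchanged. As recruitment is open, the scheduling rule is worth most if adopted early.
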